### Efficacy

2.8

Efficacy will be evaluated using a 20% or more improvement on the VAS relative to the control value at the outpatient visit 12 weeks after administration based on the self-filled VAS of patients.

(The main evaluation point is the improvement rate of 20% or more of the VAS control value at the outpatient visit 12 weeks after administration.)

### Safety

2.9

The safety evaluation indices of this clinical trial are as follows: adverse events are any undesired or unintended signs (including abnormal laboratory values, abnormal vital signs), symptoms, or illnesses that occur between the beginning of Goreisan use and the end of the last observational study. It does not matter whether the study demonstrates a causal relationship. Symptoms and diseases occurring before the use of medical devices are treated as complications and not adverse events. However, if the complications worsen after the beginning of the medical device use, they will be treated as adverse events, and the day on which the deterioration is confirmed will be the date of occurrence of the adverse events. After enrolment, if the patient discontinues taking the drug for 12 weeks during the administration of Goreisan, the study should be discontinued.

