### Study design

2.1

This multicenter, randomized, group-controlled study will involve patients treated for glossodynia. Patients with consent will be randomized and assigned to 1 of 2 groups as shown below (ratio 1:1). In the experimental group, Goreisan will be taken for 12 weeks in combination with conventional treatment, Patients in the control group will only receive the standard treatment (Western medicine administration). The study will be conducted mainly at the Nagasaki University Hospital in Japan. It is registered on the Japan Registry of Clinical Trials. It will also be conducted following the principles of the Declaration of Helsinki and the established best clinical practices of Japan.

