### Participant recruitment

2.2

Participants have been recruited from the Nagasaki University Hospital, where the subsequent study will also take place. The treating clinical research coordinator explained the study to all participants, and each participant signed an informed consent form. This is intended for patients undergoing medical treatment with the chief complaint of glossodynia. The medical institutions that will conduct research will target patients undergoing medical treatment at Nagasaki University Hospital (Oral Pain Liaison Outpatient center), Aichi Medical University Hospital, and Tokyo Medical and Dental University. The case registration and allocation organizations are Nagasaki University Hospital, Tokyo Medical and Dental University, and Aichi Medical University; each will perform case registration and allocation using REDCap. REDCap was used to randomly allocate participants to the “Goreisan-administration” and “non-Goreisan-administration” groups at a ratio of 1:1 (stratified block method).

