#### Sample size

2.2.1

In this study, ninety patients with the chief complaint of glossodynia undergoing medical treatment are targeted. A preliminary study (Okayasu I. et al, Advances in Traditional Medicine. 2020, In press) found that after 2 weeks of Goreisan administration, the degree of pain on visual analog scale (VAS) was reduced by more than 20%. Improvement was observed in 8 of 14 cases (about 57%). On the rate of pain improvement, the effective rate of the standard treatment group is 10% and the expected effective rate of this drug is 40%, with α of 0.05 and power of 0.9. The number of cases should be approximately 82 (41 in each group) because statistical analysis is possible in approximately 90 cases, in considering a dropout of approximately 10%. Therefore, the sample size is set for approximately 90 cases in total with 45 cases in each group. Each of the 3 medical institutions will be assigned 30 cases (15 cases per group).

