### Adverse events

2.6

In this study, adverse events related to the study drug (possible liver dysfunction due to long-term use of Goreisan) will be considered. During the study period, blood will be drawn and liver function tests will be performed. If there are any abnormalities, the study will be discontinued immediately and appropriate treatment will be administered.

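### Section 2.9 starts adverse-event counting at the beginning of Goreisan use, which gives the control arm no start point, so events cannot be compared between arms as defined

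*Protocol article*

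**What the plan says.** Section 2.9 (Safety) sets out the trial's safety indices. It counts undesired signs, including abnormal laboratory values and vital signs, as well as symptoms and "illnesses that occur between the beginning of Goreisan use and the end of the last observational study", and adds that a causal link is not required.

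The same section then separates pre-existing conditions from adverse events: "Symptoms and diseases occurring before the use of medical devices are treated as complications and not adverse events". The rule for conditions that worsen is tied to device use in the same way.

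Section 2.1 (Study design) describes the two arms. For the experimental arm: "In the experimental group, Goreisan will be taken for 12 weeks in combination with conventional treatment". For the other arm: "Patients in the control group will only receive the standard treatment (Western medicine administration". Section 2.2 allocates patients to the two "groups at a ratio of 1:1 (stratified block method", and section 2.2.1 plans 45 patients per group.

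Section 2.6 (Adverse events) says that "adverse events related to the study drug (possible liver dysfunction due to long-term use of Goreisan) will be considered", and then: "During the study period, blood will be drawn and liver function tests will be performed". It does not name an arm for the blood tests.

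The Discussion presents the trial as the first to establish both the efficacy and the safety of Goreisan in this condition, and gives side effects and interactions with concomitant drugs as a reason for a well-designed study.

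**The concern.** An adverse-event definition in a randomised trial needs a start point that exists for every patient. Here the start point is an event that only one arm can experience. A site following the text has no basis for deciding which control-arm events count, or from when.

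The comparator matters because Goreisan is added to conventional treatment and does not replace it. Section 1.2 itself notes that the drugs prescribed for glossodynia can cause effects such as drowsiness and dizziness. Such events can therefore be expected in the Goreisan arm whether or not Goreisan contributes. Control-arm events recorded under the same definition are what would allow a reader to tell background events from those due to Goreisan or its interaction with other drugs. Without them, the safety description becomes close to a single-arm listing, and events from the shared drugs may be attributed to Goreisan.

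**Working it through.** The article states no safety figure to reproduce, so the check applies the written definition to each arm and then looks for other text that would repair it.

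**Step 1. Apply each rule to each arm.**

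| Rule | Anchor as written | Goreisan arm | Control arm |
|---|---|---|---|
| Adverse-event window opens (2.9) | Beginning of Goreisan use | Exists | Does not exist (2.1: standard treatment only) |
| Pre-existing condition (2.9) | Use of medical devices | No device is a study treatment | No device is a study treatment |
| Worsening of a pre-existing condition (2.9) | Beginning of device use | As above | As above |
| Liver function tests (2.6) | Study period | Applies | Not excluded |

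**Step 2. Count the patients affected.** Section 2.2.1 states that "the sample size is set for approximately 90 cases in total with 45 cases in each group". The control arm is therefore 45 of 45 + 45 = 90 patients, or 45/90 = 50% of the trial.

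**Step 3. Look for another start point.** The only other time anchor in 2.9 is the device wording. In the Goreisan arm a reader can substitute the start of Goreisan, since the same section supplies it. In the control arm there is nothing to substitute. Section 2.6 gives the period for blood tests but does not define when an adverse event begins to count.

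**Step 4. Compare 2.6 with 2.9.** Section 2.6 speaks of events related to the study drug; section 2.9 says causality does not matter. Section 2.6 does not say that only drug-related events are recorded, so the two can coexist: one names an expected risk, the other gives the general definition. The article does not state that relationship. If a site took 2.6 as the operative rule, control patients would again fall outside it, because they receive no study drug.

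**Step 5. Check whether a planned analysis depends on this.** Section 2.11 (Statistical analysis) specifies Fisher's exact test for the improvement rate only. No between-arm safety test is described. The definition therefore affects the description of safety and no stated hypothesis test.

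**The case against.** The strongest reply is that the article uses Goreisan wording as shorthand for study time zero. Sections 2.7 and 2.8 time the primary endpoint at 12 weeks after administration, section 2.7.2 times the secondary endpoints after Goreisan administration, and section 2.5 describes the visits as if every patient took Goreisan. Yet section 2.11 compares improvement in both arms, so control patients must be assessed too. Read with equal literalness, those sections would leave the control arm without an endpoint date. On this view 2.9 is loose drafting, and the device wording is leftover text.

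This has force. It makes a deliberate exclusion of control events unlikely, and no section states one. It does not repair the definition, however: 2.9 is the rule that sites would apply, and different sites could supply different start points for control patients.

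A second reply is that safety is neither a primary nor a secondary endpoint and that the Introduction states the purpose in terms of pain; the safety aim appears in the Discussion. That is fair and limits the severity. The article still gives a definition and a safety aim, and the first does not serve the second. Because the fault lies in what 2.9 states, it is not merely detail left to a fuller document.

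A reader might also infer that 45 patients will contribute no safety data at all. The documents do not support that. The liver tests in 2.6 are not restricted to one arm, and Table 1 and the supplementary list of collected items, which might show what is recorded in each arm, are not available here.

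**Conclusion.** The point holds as a defect of definition. As written, section 2.9 gives about 45 of 90 patients, the whole control arm, no adverse-event start point, and its rules for pre-existing and worsening conditions rest on an anchor foreign to this trial. A between-arm comparison of adverse events under that definition is undefined. This should be fixed, but it does not threaten the primary analysis.

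The conclusion rests on reading 2.9 and 2.1 as they stand, and on the assumption that Table 1 and the supplement do not give a separate start point for control patients.

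Three stronger readings go too far. A reader might infer that the control arm would be tabulated with zero events, producing a falsely significant excess on Goreisan. An undefined window yields no valid control count or denominator, not a zero; no safety test is planned; and the article gives no event rate from which to size such an effect. A reader might infer that 2.6 contradicts 2.9 outright; it does not, since 2.6 never says that only drug-related events count, and clarification is enough. Finally, a reader might infer that the Goreisan arm also lacks any start date; the beginning of Goreisan use supplies a workable one there.

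**What to change.** Amend 2.9 and 2.6 as follows:

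- Define adverse events in both arms as any untoward event from one arm-neutral start point, for example randomisation, to the last observation at week 12, regardless of causality.
- Use the same start point for pre-existing conditions and for worsening, and delete the device wording.
- State in 2.6 that the reference to drug-related events names an expected risk and does not narrow the definition in 2.9.
- Tabulate adverse events and liver test results by randomised arm. Descriptive counts are sufficient; no formal test is needed.

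Starting at randomisation will pick up any events between allocation and the first dose in the Goreisan arm. The same rule applies to controls, so the comparison stays even-handed.

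The cost is small changes to the protocol and case report form and some extra recording in the control arm. The comparison in 2.11 requires control patients to be assessed at week 12; that they also attend at weeks 4 and 8 is likely but not stated, so the control visit schedule should be confirmed. The change is best made early, because control-arm events not recorded as they occur are hard to recover later.

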### Study protocol

2.5

Patients who have provided consent should be visited in advance, and the degree of pain and saliva at that time will be assessed. After that, Goreisan will be taken at 7.5 g/d (minute 3) for 12 consecutive weeks. Four weeks later, the patients will return to the hospital for a second assessment of pain and saliva. Eight weeks after this, the patients will be reexamined, and the third assessment of pain and saliva will be performed. Twelve weeks after the first test, a fourth test will be performed.

During each outpatient consultation, the weather conditions, such as temperature, humidity, and barometric pressure, should be recorded and displayed on the outpatient meteorometer on the chart. Patients should also observe, and possibly record, the degree of pain at home, in addition to assessments during their visit to the outpatient clinic at a medical institution (Table 1).

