### Outcome

2.7

The primary endpoint is the 20% or more improvement on the VAS relative to the control value at the outpatient visit 12 weeks after administration based on the self-filled VAS of patients.

(The main evaluation point is the 20% or more improvement in the VAS control value at the outpatient visit 12 weeks after administration.) (All itmes to be collected as listed in SDC).

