#### Rationale for an improvement rate of 20% or more

2.7.1

The degree of pain will be evaluated using VAS. Regarding the determination of VAS based on subjective symptoms, those with a decrease of 20% or more are “improved,” and the other cases are “not improved.”

The grounds for improving the VAS entered by the patient by 20% or more are as follows. This criterion was based on previous drug information for celecoxib (KEGG Drug Databese), using the 20% improvement criterion used by the American College of Rheumatology. For this criterion, patients with a 20% or greater improvement in pain perception (VAS) were considered valid cases when assessing the efficacy of celecoxib. In the clinical trial that evaluated the clinical outcomes of celecoxib for rheumatoid arthritis pain, assessments were performed using the American College of Rheumatology improvement rates (various methods), and the results provided drug information for treating patients with a VAS improvement of 20% or more. This standard was adopted for pain improvement following the administration of Goreisan.

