### Statistical analysis

2.11

The difference between the improvement rate between the Goreisan administration group and the non-administration standard treatment group will be analyzed by Fisher exact test. Test the null hypothesis: there is no difference between the rates of improvement of the Goreisan administration group and the standard treatment group.

In addition, the degree of pain will be evaluated using VAS. The verdict for VAS based on subjective symptoms, which is reduced by 20% or more, is “improved,” and the others are “non-improved.” The grounds for improving a VAS that has been reduced by more than 20% from the target value entered by the patient are as follows.

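### Section 2.9, on its workable reading, takes a patient out of the study when Goreisan stops; only the Goreisan arm can lose its week-12 VAS this way, with a bias of unfixed direction and modest size

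*Protocol article*

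**What the plan says.** Section 2.9 (Safety) ends with the instruction that "if the patient discontinues taking the drug for 12 weeks during the administration of Goreisan, the study should be discontinued". Section 2.1 (Study design) gives Goreisan to the experimental arm for 12 weeks on top of conventional treatment, while "Patients in the control group will only receive the standard treatment (Western medicine administration").

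The primary outcome depends on one late reading. Section 2.5 (Study protocol) places it: "Twelve weeks after the first test, a fourth test will be performed". Section 2.7 (Outcome) defines success as a 20% or greater "improvement on the VAS relative to the control value at the outpatient visit 12 weeks after administration". Section 2.11 (Statistical analysis) compares the two improvement rates by Fisher's exact test.

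Two parts of the article bear on what happens to a patient without that reading, and they point in different directions. Section 2.2.1 (Sample size) arrives at "approximately 82 (41 in each group) because statistical analysis is possible in approximately 90 cases, in considering a dropout of approximately 10"%, which suggests that dropouts are not analysed. Section 2.7.1 sorts patients into those with the required fall "and the other cases are “not improved", and Section 2.11 repeats the split: "which is reduced by 20% or more, is “improved,” and the others are “non-improved". Taken literally, these two would count a patient with no week-12 reading as a failure.

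Section 2.6 (Adverse events) also ends the study on an abnormal liver test. It does not say whether that means the drug, the patient's follow-up or the trial.

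**The concern.** A rule triggered by stopping Goreisan has no counterpart in the control arm. Controls can be lost for other reasons, but not for this one. If stopping the drug ends follow-up, what happens with treatment in one randomised arm decides whether the primary outcome is collected there. Stopping may well be related to tolerability or lack of benefit, so the patients lost need not resemble those who remain.

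Two things are at stake. The more certain is an avoidable loss of primary data in one arm: a later analysis plan can impute or classify a missing reading but cannot recover it. The less certain is a shift in the comparison, which depends on who stops and how they are then handled. The wording is also hard for three sites to apply in the same way.

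**Working it through.** **1. Which reading can be applied?**
- A 12-week interruption within a 12-week course would apply only to someone who took essentially none of the drug.
- Closing the whole trial because one patient stops is not a workable rule.
- Ending the drug only is circular, since the trigger is that the patient has already stopped it.
- Ending that patient's participation remains.

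**2. Inputs.** Section 2.2.1: "the effective rate of the standard treatment group is 10% and the expected effective rate of this drug is 40"%, alpha 0.05, power 0.9, 41 per group evaluable, 45 per group recruited. Section 2.11: Fisher's exact test; two-sided is assumed from the null hypothesis of no difference. The article gives no stopping rate by arm. I assume 5 stoppers of 45 (11%), close to the planned dropout of about 10%.

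**3. The plan's own figure.** Two-sided pooled formula without continuity correction, mean rate 0.25:

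n = [1.960·√(2·0.25·0.75) + 1.282·√(0.10·0.90 + 0.40·0.60)]² / 0.30² = (1.200 + 0.736)² / 0.09 ≈ 41.7, so 42 per arm. The stated 41 agrees within rounding, and 82/0.9 ≈ 91 agrees with about 90.

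**4. Shift in the Goreisan rate.** With true rate p and 5 stoppers improving at rate s, all left out, the observed rate is (45p − 5s)/40.

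| True p | s = 0 | s = p/2 | s = p |
|---|---|---|---|
| 40% | 18/40 = 45.0% | (18 − 1)/40 = 42.5% | 40.0% |
| 10% | 4.5/40 = 11.3% | (4.5 − 0.25)/40 = 10.6% | 10.0% |

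At 40% vs 10% with s = 0, the expected difference goes from 30 to 35 points. If 4 control non-improvers are also lost, the control rate is 4.5/41 = 11.0% and the difference is 34 points.

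In the other direction, if all 5 stop because they have improved, the Goreisan rate is (18 − 5)/40 = 32.5% and the difference 22.5 points.

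If 5 non-improving stoppers stay in the denominator as not improved, the rate is 18/45 = 40% and there is no upward shift.

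**5. Type I error.** Exact enumeration of two binomials, two-sided Fisher at p ≤ 0.05, equal true rates of 10%:
- 45 vs 45, nobody lost: 2.0%
- 40 vs 45, no selection: 3.2%
- 5 Goreisan non-improvers removed: 3.8%
- 5 Goreisan and 4 control non-improvers removed: 3.2%
- 5 and 5 removed: 2.0%
- 9 and 0 removed: 4.2%

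Of the 1.8-point rise from 2.0% to 3.8%, about 3.2 − 2.0 = 1.2 points arise because unequal group sizes make Fisher's test less discrete. About 3.8 − 3.2 = 0.6 points come from selective loss. Every 10% scenario stays below 5%.

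At common rates of 25% and 40%, assumed only to show the range, removing 5 Goreisan non-improvers gives 5.0% and 6.1%, against 3.7% and 3.9% for 40 vs 45 without selection.

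**6. Power if stoppers are kept.** Fisher power at 40% vs 10% with 45 per arm is 88.9%. If 40% was meant for completers only and 5 stoppers do not improve, the as-randomised rate is 0.40·40/45 = 35.6% and power is about 78%.

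**The case against.** The strongest reply is that Section 2.9 nowhere says visits cease or that the week-12 VAS is not taken. It is a loosely worded section that even refers to medical devices in a drug trial, and a one-arm rule should not be built on one poor sentence. That stands as a caution about confidence. It does not remove the point, because the other readings are unworkable or circular, and each would still leave an instruction that sites could apply differently.

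The second reply is that an upward bias needs several conditions together: stoppers do not return at week 12, are mainly non-improvers, are left out of the analysis, and are not matched by similar control losses. None is stated. The wording of Sections 2.7.1 and 2.11 may count them as failures, and the step from 82 to 90 is ordinary recruitment inflation that defines no analysis set. This stands, and it is why the direction is left open.

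Third, most of the rise in type I error at the 10% rate is an effect of group size. That also stands.

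Fourth, the analysis set and missing-data rules belong to a statistical analysis plan that is not shown. Agreed; neither is claimed as missing here. Whether the reading is collected at all is a matter of trial conduct, which the protocol sets.

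**Conclusion.** The point holds as a stated rule that should be repaired, with medium confidence because it rests on the workable reading of a garbled sentence. The rule can act only on the Goreisan arm and can cost it primary outcome data for a treatment-related reason.

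The size is modest and conditional. In the adverse case assumed here (5 of 45 lost, none improved, all excluded, no control losses), the planned difference is overstated by 5 points. Under no effect at 10%, the Goreisan rate is overstated by 1.3 points.

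A reader might infer that the plan is biased in favour of Goreisan or that its false-positive rate is out of control. The documents support neither. They give no stopping rate, do not say who stops and do not settle how stoppers are classified. The bias may be zero or run against Goreisan, and at the plan's own control rate the type I error stays below 5% in every scenario computed. A reader might also take Section 2.6 as a second one-arm rule. It is not limited to one arm and matters here only for its wording.

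**What to change.** Reword Section 2.9, for example: *A patient who stops Goreisan for any reason stops the drug only, stays in the study and completes the VAS at weeks 4, 8 and 12.* Word Section 2.6 in the same way, so that an abnormal liver test stops the drug and not the VAS follow-up. Which abnormalities should stop the drug remains a clinical decision for the investigators. The analysis set and the handling of any VAS still missing can be left to the statistical analysis plan.

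The direct cost is amendment wording and a few more VAS forms. There may also be a cost in power. If the planned 40% described completers only, keeping 5 non-improving stoppers takes power from about 89% to about 78%, so the sponsor should confirm which population that rate refers to.
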